**Study Objectives and Hypotheses**

This 2-year randomized controlled trial proposes to use multiple, longitudinal quantitative measures to assess the impact of CATCH ED on health outcomes and acute care service utilization for frequent users of ED (>5 visits/yr) 12 months after program enrolment. By better coordinating health and social services and by making diverse services more readily available in the community, CATCH-ED will offer frequent users a full array of services and good continuity of care. We hypothesize that continuity of community-based care will be associated with better health outcomes and decreased reliance on Emergency Department use and days in hospital during the 12-month follow up period.

The primary research question is: Is a brief case management intervention program (CATCH-ED) effective in reducing ED visits for frequent users of EDs (>5 ED visits in the past 12 months)? The primary measure of effectiveness is the reduction in ED use, 12 months after program enrolment.

The secondary research question is: Is the intervention effective in improving health outcomes for frequent users of EDs (>5 ED visits in the past 12 months)? The secondary measures of effectiveness are changes in: 1) inpatient care utilization; 2) health status; 3) mental health; 5) substance use; 6) quality of life and 7) service satisfaction, 12 months after program enrolment.

Furthermore, an economic evaluation will be completed by the AHRC. The objective of the economic evaluation is to compare the cost-effectiveness of the CATCH-ED intervention with usual care, using patient-level data from the randomized clinical trial and linked administrative data at the Institute for Clinical Evaluative Sciences (ICES), Toronto.

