**Methods - Outcome Evaluation**

The study design is a randomized controlled trial in which multiple longitudinal outcome measures will be collected on both the intervention and control groups to assess client characteristics and selected outcomes of interest.

Frequent users will be recruited to the study over a 9-month period and followed for 12 months. Program participants will complete survey interviews at baseline, 6 and 12 months to assess health status, mental health, substance use, self reported acute care service use, service satisfaction and their working alliance with their primary clinician. Self-reported acute care use will be complemented by administrative data linkage to examine acute care service use 12 months prior and 12 months following referral to the intervention. Participants will also complete survey interviews at 3 and 9 months to assess their service use and to confirm their contact information and any time spent outside the Province during the previous three-month period.

*Sample Size Calculation*

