**Analysis Plan**

We will calculate descriptive statistics (mean, standard deviation, quartiles) and construct graphs (histograms, scatter plots, box-plots) to characterize the clients at baseline with respect to socio-demographic factors, housing status, health status, and health service use. Baseline group comparisons will be conducted using chi-square test or Fisher’s exact test (for categorical variables), t-test or Wilcoxon rank-sum test (for continuous variables). We will construct plots to describe longitudinal changes in primary and secondary outcomes over time. All analyses will use an intent-to-treat perspective and will be compared with a per-protocol analysis. The primary outcome evaluates the proportional change in rate of emergency department visits (ED visits) between pre-intervention and 6-month time intervals post-intervention; some secondary outcomes (number of hospitalizations, days in hospital) are also count measures, negative binomial outcomes will be compared with Poisson regression accounting for overdispersion to determine the overall treatment effect. While it is usually customary to match the sample size calculation technique to analysis approach, in this case insufficient published data is available to calculate a sample size for a marginal techniques (Generalized Estimating Equations - GEE) that is proposed as our primary analytic technique. While GEE models represent the main question being studied (the impact of the intervention on population measures of ED use), conditional models can also provide useful information and sample size techniques require fewer assumptions. For this reason, both marginal and conditional (random effects models) will be fit and compared during the data analysis phase of this study. The choice of the most appropriate representation of the overdispersion of data (Negative binomial versus the use of an overdispersion factor in a poisson regression) is highly dependent on the variance structure observed in the collected data (Ver Hoef & Boveng, 2007); hence, the covariance estimates of the observed data will inform final model selection. GEE and mixed effects models will be compared to account for the repeated measurement of participants. A literature review and the presence of clinically significant differences in baseline data will determine which, if any, covariates require adjustment in the final model, and these will be included as covariates in the generalized linear regression models. Other secondary normally distributed outcomes (quality of life, service satisfaction) with be analysed using linear regression using the same principles of adjustment for clinically important covariates, and marginal versus conditional approaches.

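### The plan does not commit to adjusting continuous secondary outcomes for their own baseline value, and ties adjustment partly to observed baseline differences

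*Protocol*

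**What the plan says.** The Analysis Plan sets its covariate rule while describing the count models: "A literature review and the presence of clinically significant differences in baseline data will determine which, if any, covariates require adjustment". It then carries the rule over to the continuous secondary outcomes, which "with be analysed using linear regression using the same principles of adjustment for clinically important covariates, and marginal versus conditional approaches". That sentence names quality of life and service satisfaction as its examples and no other scale. On repeated data, the same section says that "GEE and mixed effects models will be compared to account for the repeated measurement of participants". It does not say whether the baseline score is a response or a covariate in those models.

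The baseline scores will exist. Under Methods - Outcome Evaluation, "Program participants will complete survey interviews at baseline, 6 and 12 months to assess health status, mental health, substance use", and service satisfaction is in the same interviews. The Randomization process paragraph places the baseline interview before allocation, so each score is a valid covariate.

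Two other places bear on the point. Study Objectives and Hypotheses words the effects as change: "The secondary measures of effectiveness are changes in: 1) inpatient care utilization; 2) health status; 3) mental health", and the list goes on to quality of life and service satisfaction. The Economic Evaluation Plan lists baseline utility among the terms of its cost and QALY regressions and attaches no condition about imbalance.

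**The concern.** The reason to adjust a scale for its own baseline is that the baseline score predicts the follow-up score. Adjustment removes that predictable part from the residual variance, and does so just as well when the arms happen to match. A rule that looks for clinically significant baseline differences can therefore drop the score in the very case where the arms look alike, although the gain is still available. It also makes the model depend on the observed data.

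The secondary research question, whether the programme improves health outcomes, rests on the interview measures along with inpatient use. The sample size was set for ED visits only, and attrition of up to 30% is expected. Administrative records can fill gaps in ED visits but not in interview scales. These outcomes have little precision to spare, and wider intervals make it more likely that a real benefit is reported as not shown.

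**Working it through.** **The plan's own figures.** The protocol gives no sample size, effect size or power for the interview scales. The 64 per arm under Sample Size Calculation is for a 20% reduction in ED visit rate. It cannot be reproduced, because alpha, power, visit rates and dispersion are not stated. The recruited 83 per arm matches 64 x 1.3 = 83.2. With 30% attrition, 83 x 0.7 = 58.1, so about 58 per arm would be interviewed at the end.

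**Assumptions.** Rho is taken as 0.3 to 0.7. The only related figure in the protocol is the Colorado Symptom Index test-retest value of .71, which is not a 12-month correlation and serves at most as a rough upper guide. The effect is taken as 0.5 SD, with two-sided alpha 0.05. The SD is taken as equal at baseline and follow-up, and the relation as linear.

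**Formulas.** With v the variance of the treatment difference relative to a follow-up-only comparison:

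- follow-up only: v = 1
- change score: v = 2(1 - rho)
- adjusted for baseline: v = 1 - rho^2
- power = Phi(0.5 / sqrt(2v/n) - 1.96)
- detectable difference at 80% power = (1.960 + 0.842) x sqrt(2v/n)

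**Variance relative to the adjusted analysis.** Follow-up only is 1/(1 - rho^2). Change score is 2(1 - rho)/(1 - rho^2) = 2/(1 + rho).

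| rho | Follow-up only | Change score |
|---|---|---|
| 0.3 | 1/0.91 = 1.10 | 2/1.3 = 1.54 |
| 0.5 | 1/0.75 = 1.33 | 2/1.5 = 1.33 |
| 0.7 | 1/0.51 = 1.96 | 2/1.7 = 1.18 |

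**Power for 0.5 SD, and detectable difference in SD units, with 58 per arm.** Here sqrt(2/58) = 0.186, so follow-up-only power is Phi(2.69 - 1.96) = Phi(0.73) = 76.8%.

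| rho | Follow-up only | Change score | Adjusted |
|---|---|---|---|
| 0.3 | 76.8%; 0.52 | 62.4%; 0.62 | 80.6%; 0.50 |
| 0.5 | 76.8%; 0.52 | 76.8%; 0.52 | 87.5%; 0.45 |
| 0.7 | 76.8%; 0.52 | 93.5%; 0.40 | 96.5%; 0.37 |

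Put as sample size, adjusting 58 per arm is worth 58/(1 - rho^2) = 64, 77 or 114 per arm analysed without baseline. With no attrition (83 per arm) and rho 0.5, power is 89.6% without baseline and 96.1% with it.

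**Baseline as a repeated response.** If a longitudinal model gives each arm its own baseline mean, then with complete data and an unstructured covariance the treatment-by-time contrast at 12 months is the difference in mean change. It has the change-score precision. If the model imposes one common baseline mean, which randomisation justifies, essentially nothing is lost against baseline adjustment.

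**The case against.** The strongest reply is that the protocol leaves baseline open rather than leaving it out. The score could enter in three ways: the literature review could select it as a known predictor, it could be used through change scores as the objectives are worded, or it could be one of the repeated responses in the GEE or mixed models. Covariate lists are commonly left to a statistical analysis plan, and none is at hand.

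Much of this stands. A reader might infer that the stated regression excludes the baseline score and that a loss is certain; the text supports neither. A reader might also extend the sentence to health status and symptom scales, but it does not name them, and they are covered only if analysed the same way. Nor is there a bias claim: randomisation keeps the unadjusted estimate unbiased apart from missing data, and its standard error already reflects chance imbalance.

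The size is also open to challenge. At rho 0.3 the gain over follow-up only is 3.8 points of power, and at rho 0.7 the gain over change scores is 3.0 points. The 58 per arm takes the maximum attrition and ignores the planned imputation. For service satisfaction, the baseline rating concerns care received before the programme, so rho may be low.

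What does not stand is the argument from silence. The protocol states a selection rule and applies it to these outcomes, and a later plan that followed it could properly fit no baseline covariate. Change scores and an unconstrained repeated response do not cure the loss. Below rho 0.5, a change score is less precise than ignoring baseline altogether, since 2(1 - rho) then exceeds 1.

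**Conclusion.** The point holds as a failure to commit, combined with a poor trigger. For the normally distributed secondary outcomes, whether the scale's own baseline value is used depends on a literature review and on observed clinically significant differences, although the benefit depends on neither imbalance nor its size.

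If baseline is left out, or enters only as a change score or an unconstrained response, precision is lost. For rho of 0.3 to 0.7, the variance is 1.10 to 1.96 times (follow-up only) or 1.54 to 1.18 times (change score) that of the adjusted analysis. At the middle of that range, with 58 per arm and a 0.5 SD effect, power is about 77% instead of 87.5%. Rho and the effect size are assumptions that the protocol does not supply.

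The primary ED-visit analysis and the economic regressions are not affected. This is worth correcting because the remedy is nearly free, not because the secondary results would be invalid without it.

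**What to change.** In the Analysis Plan, state that each continuous secondary outcome measured at baseline is analysed with its own baseline value as a covariate, whatever the observed baseline difference. The Economic Evaluation Plan already treats baseline utility this way. A longitudinal model with a common baseline mean across arms is an equivalent choice. Name the scales to which the sentence applies, since it now lists only two, and say that change in the objectives is estimated in this way and not by raw change scores. The literature-review rule can stay for any further covariates.

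The cost is a sentence or two of text and one or two degrees of freedom per model. The baseline interview already precedes randomisation, so no new data or participants are needed. For service satisfaction the gain may be small, but so is the cost.

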This model draws from the experience of the Coordinated Access to Care for the Homeless (CATCH Homeless) program, a made-in-Toronto variant of a Critical Time Intervention (CTI) model that provides transitional support to homeless people with complex, unmet health care needs in the community. The adapted CTI model includes three phases. During Phase 1 (month 1) program goals include assessing participant needs, strengths and resources, providing practical needs assistance and developing individualized treatment and support plans; Phase 2 (months 2-3) is focused on ongoing assistance and on facilitating and testing connections/referrals to appropriate long term community based supports; in Phase 3 (months 3-4) care is transferred to the support network developed during phase 2. Program activities include home visits and assertive outreach, introduction of participants to new service providers and discussion of the comprehensive care plan with all members of the support network. Furthermore, transitional case managers offer crisis intervention, supportive therapy, and assistance in obtaining income support and housing. CATCH-ED will serve to expand CATCH to increase the range of populations served; the range of services offered (e.g., team-based primary care in CHC and FHT settings, trauma-informed group services, and solution-focused therapy/support provided in non-ED settings); and possibly, the range of technologies used to connect and keep people connected with care providers (e.g., home/community-based monitoring of co-morbid medical conditions; use of portable telemedicine equipment to support nurses in the community; and telemedicine-facilitated consultation with psychiatrists). The CATCH-ED program model provides transitional case management support over 3-4 months, offering timely, potentially cost-effective access to needed services in a coordinated way.

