*Longitudinal Follow -Up*

Study participants will be interviewed at baseline, 3, 6, 9 and 12 months following program enrolment. The study protocol requires face-to-face interviews at each of the five time points. Study participants will receive a payment of $50 for the baseline, 6 and 12 month interviews (duration of one hour) and $25 for the 3 month and 9 month follow up interviews (duration of 15 mintues). Study participants will be followed intensely by a research assistant, especially trained in locating and contacting individuals with mental health and addictions problems. Baseline interviews will be completed within two weeks of program referral. There will be a four-week window for data collection at the 3-month, 6-month, 9-month and 12-month time points. Interviews will be conducted between two weeks prior to and after the scheduled follow up date. Data will be considered missing for the particular time point if the participant is not interviewed within the interview windows. Research assistants will contact participants each month to confirm contact information. Additional strategies to minimize study attrition will include collecting names and phone numbers of family ,and /or acquaintances and /or service providers (with participant consent) to help maintain participant contact.

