
Given the possibility of missing data in following participants for 12 months who may have unstable housing or community connections, imputation methods will be used to estimate the overall impact of missing data on outcomes. Administrative data from the Institute of Clinical and Evaluative will be used for the purposes of evaluating the primary outcome, and comparing the impact of missing data on outcomes.

*Economic Evaluation Plan*

The objective of the economic evaluation is to compare the cost-effectiveness of the CATCH-ED intervention with usual care, using patient-level data from the randomized clinical trial and linked administrative data at the Institute for Clinical Evaluative Sciences (ICES), Toronto. The Ontario MOHLTC perspective will be used in the analysis. In Ontario, the Ministry pays for physician visits, laboratory tests, imaging, hospitalization, emergency department visits, same day surgery/ procedure, complex continuing care and some home care services. In addition, the Ministry pays for prescription drugs for those older than 65 years old, live in a Long-Term Care Home or a Home for Special Care or enrolled in special programs such as the Ontario Disability Support Plan (ODSP). The time horizon for the economic evaluation will be 12 months (maximum follow-up of the trial).

The primary outcome will be the incremental cost per quality-adjusted life-year (QALY) gained though the intervention compared with usual care. The secondary outcomes include the incremental cost per ED visit avoided and incremental cost per hospital-day avoided.

Measuring QALYs: A QALY is a year of life experienced with a particular health-related quality of life (HRQoL) or health state utility, as represented on a scale from 0 to 1, where 0=death and 1=full health. The EQ-5D and SF-6D (converted from SF-12), generic preference-based instruments that have been used in mental health patients, will be used to assess patients’ health state utility at baseline, 6 months and 1 year. We will calculate each patient’s QALY from the utility scores using the area-under-the-curve approach, with linear interpolation between assessment points (Figure 1).

[figure not shown]

QALY0-90 days

QALY6 -12 months

QALY0-6 months

Figure 1. Calculating QALYs from EQ-5D utility scores

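### Utility for the primary economic outcome is not measured during or at the end of the 3-4 month programme, so interpolation from baseline to 6 months can mis-state the QALY difference in a direction the planned data cannot show

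*Protocol*

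**What the plan says.** Protocol, Economic Evaluation Plan: "The primary outcome will be the incremental cost per quality-adjusted life-year (QALY) gained", over a 12-month horizon. The EQ-5D and the SF-6D (derived from the SF-12) give "health state utility at baseline, 6 months and 1 year". Each participant's QALYs come from the "area-under-the-curve approach, with linear interpolation between assessment points".

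Methods - Outcome Evaluation gives the same schedule: "Program participants will complete survey interviews at baseline, 6 and 12 months to assess health status". The 3- and 9-month interviews cover service use, contact details and time spent outside the Province, but not health status.

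The Intervention describes "transitional case management support over 3-4 months".

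Longitudinal Follow-Up: "The study protocol requires face-to-face interviews at each of the five time points". The 3-month interview is therefore already planned in person; it lasts 15 minutes and is paid.

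The surviving Figure 1 labels name three QALY segments: 0-90 days, 0-6 months and 6-12 months.

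**The concern.** The programme is over by month 3 or 4, and the next utility measurement is at month 6. Everything between baseline and month 6 is a straight line, and that stretch is half of the 12-month horizon. If participants' health state improves while a case manager is active and falls back afterwards, the straight line passes beneath the improvement. If the effect appears only once community supports are in place, the line credits a gain that had not yet occurred. Either way the error goes into the QALY difference, which is the denominator of the primary economic outcome.

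This cannot be left to a statistical analysis plan. The protocol fixes the measurement schedule, and no later analysis can recover a utility that was never collected.

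The Figure 1 labels add an inconsistency. A 0-90 day segment lies inside the 0-6 month one, and the stated schedule has no utility assessment at 90 days.

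**Working it through.** The protocol states no utility or QALY figure, so there is nothing of the plan's own to reproduce.

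**Inputs from the protocol.** Utility at 0, 6 and 12 months with linear interpolation (Economic Evaluation Plan); programme length 3-4 months (The Intervention); an interview at 3 months (Longitudinal Follow-Up).

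**Assumptions.** Let g(t) be the between-arm difference in mean utility, with g(0) = 0 because of randomization. G is the full size of the gain. The documents do not give it; 0.03 to 0.10 is used as an assumed range. The 0/3/6/12 schedule serves as the reference, although it is itself interpolated between its points.

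**Formulas (trapezoid rule, time in years).**

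- Planned, 0/6/12: 0.25 × g6 + 0.25 × (g6 + g12)
- With a 3-month value, 0/3/6/12: 0.125 × g3 + 0.125 × (g3 + g6) + 0.25 × (g6 + g12)
- Amount missed = second minus first = 0.25 × g3 − 0.125 × g6 = 0.25 × (g3 − g6/2)

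The planned line already credits g6/2 at month 3. The error is the departure of g3 from that value, multiplied by a quarter of a year.

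**Results for G = 0.05 (assumed).**

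| Path of the gain | g3, g6, g12 | Planned | With 3-month value | Captured |
|---|---|---|---|---|
| Gone by 6 months | G, 0, 0 | 0 | 0.0125 | 0% |
| Half kept at 6, gone by 12 | G, G/2, 0 | 0.0125 | 0.0219 | 57% |
| Held to 6, gone by 12 | G, G, 0 | 0.0250 | 0.0313 | 80% |
| Held to 12 | G, G, G | 0.0375 | 0.0438 | 86% |
| Linear rise to 6, then held | G/2, G, G | 0.0375 | 0.0375 | 100% |
| None at 3, full from 6 | 0, G, G | 0.0375 | 0.0313 | 120% |

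Worked example, second row: planned = 0.25 × 0.025 + 0.25 × 0.025 = 0.0125. With the 3-month value = 0.125 × 0.05 + 0.125 × 0.075 + 0.25 × 0.025 = 0.0219. The ratio is 0.57.

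The captured shares do not depend on G. The absolute amounts scale with it: for G from 0.03 to 0.10, the QALYs missed run from 0.0075 to 0.025 when the gain is gone by month 6, and from 0.00375 to 0.0125 when it is held to month 12. With late onset the overstatement runs from 0.00375 to 0.0125.

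**Can the planned data tell these paths apart?** No. The held-to-12, linear-rise and late-onset rows have the same g6 and g12, and so give the same planned result of 0.0375. The reference values range from 0.0313 to 0.0438.

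**The case against.** The strongest defence is that the schedule is coherent (the health survey and the economic plan agree on 0, 6 and 12 months) and that the protocol's own mechanism does not predict an early peak. Phases 2 and 3 build a support network and hand care over to it, and Study Objectives and Hypotheses expects benefit from continuity of community care across the 12-month follow-up. The California programme cited in the Background had larger effects in its second year than in its first. Under a lasting or growing effect the planned schedule loses little or nothing. This stands, and it is why no direction of bias can be asserted.

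Four stronger readings are tempting, and the protocol does not support them.

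- A reader might infer that interpolation misses every gain made during the programme. It does not: it credits half the 6-month difference at month 3. All of a 3-month gain is lost only if it has gone by month 6 and does not return.
- A reader might infer a large multiple of error in the cost-effectiveness ratio. A path of 0.10, 0.02 and 0 at 3, 6 and 12 months gives 0.010 planned against 0.0325, a factor of 3.25. Those values are chosen for early decay; the protocol supplies none of them.
- A reader might infer that the full programme cost is set against a truncated benefit, making the intervention look less cost-effective. Table 1 has no line for programme delivery, and Potential Impact anticipates lower health care costs, so even the sign of the incremental cost is open.
- A reader might infer from Figure 1 that the first 90 days would be counted twice, or that a 90-day assessment was intended. The figure is not available, and the text nowhere says to sum the three labelled segments. The label is an inconsistency to reconcile and proves neither.

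The consequence is also limited in scope. ED visits, cost per ED visit avoided and cost per hospital-day avoided do not use utility.

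**Conclusion.** The point holds as a design weakness in the primary economic outcome. No utility is observed during or at the end of the programme, and the planned QALY difference departs from one using a 3-month value by 0.25 × (g3 − g6/2). Across the paths examined, the plan captures from 0% to 120% of that reference; for a gain that is present at month 3 and held to month 12 the figure is 86%. The shares rest on the assumed shapes and on g(0) = 0, and the absolute QALY amounts also on the assumed G of 0.03 to 0.10. The sign is unknown, and the planned data cannot reveal it.

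Separately, the 0-90 day label in Figure 1 conflicts with the stated assessment times and needs correcting whichever schedule is kept. This is a worthwhile, inexpensive improvement; it does not invalidate the plan.

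**What to change.** 1. Add the EQ-5D (five three-level items and the visual analogue scale) to the existing face-to-face 3-month interview.
2. Compute the EQ-5D area under the curve over the non-overlapping segments 0-3, 3-6 and 6-12 months.
3. Report the EQ-5D result on the 0/6/12-month schedule as a sensitivity analysis. The SF-6D would still be available only at those times, so this comparison separates a difference between instruments from a difference in schedule.
4. Correct the Figure 1 labels to match these segments.

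The argument concerns month 3 only. It gives no reason to add utility at 9 months or to prefer one instrument as the base case.

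The cost is a few minutes of extra respondent burden in a 15-minute interview, and one further eCRF page. If the 3-month EQ-5D cannot be added, remove the 0-90 day label and state the interpolation limitation when the cost per QALY is reported.
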